#### Changes in engagement in rehabilitation programmes and changes in scores of outcome measures (Table 1)

The Manager of Offender Services & Programs (MOSP)/Manager Offender Development (MOD) in each centre will play an integral part in the rollout and overall coordination. The MOSP/MOD has responsibility for case management in each centre and the selection of prisoner suitability for programmes. The Project Officers will liaise with the MOSP/MOD and collect the data on improved engagement in programmes. Data are routinely kept on programme completion and attrition, which will be used as a proxy for engagement.

#### Post-release benefits: changes in recidivism (Table 2)

The NSW Bureau of Crime Statistics and Research’s Reoffending Database (ROD) was developed to investigate reoffending. It is an identified, internally linked dataset containing records of all finalised court appearances in the Local, District and Supreme Courts of NSW since 1994. An individual’s recorded aliases are also included. The internal matching process of this database has been previously validated. Key variables include sex, month and year of birth and offending history (e.g. principal offence type, offence date, median sentence ranking [offence seriousness], number of concurrent offences, number of court appearances with at least one prison penalty, number of court appearances for a violent offence). The ROD will be used to measure categories of post-release of reoffending, given this database is a sensitive measure which is independent of public policy and incarceration rates. The number, severity and frequency of re-offences will be quantified. Recidivism rates for categories of offence will be calculated over a 2-year period for those participants who have been released. Potential for long-term benefits of omega-3 supplementation has been previously suggested in a double-blind randomised controlled trial where with a 12-week omega-3 intervention, followed by no supplementation for 12 months, 5% in the omega-3 group while 28% in the control group transitioned to psychotic disorders [58].

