## Methods: participants, interventions and outcomes

### Study setting

The study will take place in New South Wales and South Australia in Australia in at least 6 Correctional Centres. The Correctional Centres contain between 400 and 1000 prisoners including minimum, medium and maximum security. List of study sites can be obtained in the trial registration (http://www.anzctr.org.au/trialSearch.aspx) and enter ACTRN12618001665224.

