**Fig. 1 Fig1:**
[figure not shown]
CONSORT 2010 flow diagram

Exclusion criteria include (1) those prisoners due to leave prison within 16 weeks, (2) prisoners with a baseline IBOS equal to or less than 0, (3) prisoners on blood thinning agents and/or not medically fit and (4) prisoners with an erythrocyte omega-3 index of greater than 6% of total erythrocyte fatty acids.

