### Confidentiality {27}

The Correctional Officers seconded to the research study as Project Officers will enter data into two datasets: (1) a re-identifiable dataset that contains personal information and the study participants’ unique identifier code and (2) a de-identified dataset, where all the collected data from the research trial is entered. The re-identifiable dataset will be held in Correctional Services Head Office and will be used for assessing rates of recidivism. The de-identified dataset will be held with the researchers. The data files will be kept in secure locations at the UOW with appropriate back-up.

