We are aware of ethical considerations in research with Aboriginal and Torres Strait Islander people, including reciprocity, respect, equality, responsibility, survival and protection, spirit and integrity. Therefore, we believe that in the spirit of these considerations, it is important for Indigenous people in the institution to be given the same opportunity to take part in this research. The research does not include a focus on culturally specific issues; all people regardless of ethnicity can potentially derive benefits from the nutrients that are the focus of this research.

Informed consent will be obtained from all study participants and there will be no coercion. Each participant will be provided with a unique study code identifier. The Project Officer at each site will provide each participant with their supplements and supervise them taking the supplements, which will minimise intimidation for access to individual capsules. The Project Officer will keep one data file with the prisoners’ names and their unique study code identifier, hence ensuring confidentiality. All research data will be stored in another de-identified dataset containing the unique study code identifier, hence allaying concerns about blood data being shared.

This trial is a partnership between academic researchers, DSM Nutritional Products, and Correctional Services NSW and the Department for Correctional Services SA. The role of DSM Nutritional Products is to supply the omega-3 (algal oil) and placebo oil capsules as in-kind support, plus provide substantial cash contribution for this research. The role of Correctional Centres in NSW and SA is to provide in-kind support of personnel (MOSP/MOD) who have the responsibility for case management in each centre and the selection of prisoners for suitability for the rehabilitation programmes. The Project Officers (on secondment to this research) will liaise with the MOSP/MOD and collect the data on improved engagement in programmes. The role of the Corrective Services Assistant Commissioners (including AI LG, Deputy Commissioner, Strategic Policy and Planning CSNSW) is to take a lead role from our team to manage the translation into policy and practice as described above.

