The expected outcome is that supplementation with n-3 LCPUFA will reduce prisoner aggressive behaviour (as measured by the IBOS and the number and severity of reprimands), reduce aggressive disposition (AQ), attenuate attention deficit disorder behaviours (BADDS), reduce impulsiveness (BIS-brief), improve overall health and wellbeing (SF-36) and enhance rehabilitation programme engagement and gains. Increased and sustained attendance at Correctional Programs should ultimately reduce recidivism. The commitment by our collective team including communication expert and AI LG will ensure translation into policy and practice as described.

The significance of this research is the potential to improve mental health through nutritional supplementation while reducing the incidence of aggressive behaviour. This can contribute to reduced sentencing and time in custody as well as stress and burden on corrective services staff, including costs on corrective services. N-3 LCPUFA are considered to be the building blocks of good mental health, and they provide a low-cost (<$100 per year per person) and low-risk addition to a suite of mental health interventions in correctional centres. The Australian Institute of Criminology estimates that assaults alone cost Australia nearly $2.5 billion a year [72]. Given that between 35 and 41% of prisoners will be a recidivist within 2 years [73], any reduction in ongoing offending behaviour is likely to yield substantial social and economic benefit. The Health economist (CIE SE) will estimate the actual cost saving expected given trial effects observed as part of this project. Furthermore, the findings from this project have the potential for substantially broader benefits across social systems and for society if aggression and violent behaviour and metal health issues of prison populations are reduced.

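### The recidivism source named covers New South Wales courts only, although the trial also randomises men in South Australia, and the rate is confined to released men, a post-randomisation subset

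*Protocol article*

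**What the plan says.** The protocol article's Study setting section states: "The study will take place in New South Wales and South Australia in Australia in at least 6 Correctional Centres". Its Discussion lists "Correctional Services NSW and the Department for Correctional Services SA" among the trial partners, so South Australia is a recruiting state.

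The section on post-release benefits fixes the source of the recidivism outcome: "The ROD will be used to measure categories of post-release of reoffending". It describes that database as "containing records of all finalised court appearances in the Local, District and Supreme Courts of NSW since 1994". It then fixes who is analysed and over what span: "Recidivism rates for categories of offence will be calculated over a 2-year period for those participants who have been released". The start of the two years is not given.

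Table 1 leaves the method for recidivism blank and names only an investigator and Corrective Services Head Office as responsible. The Confidentiality section adds: "The re-identifiable dataset will be held in Correctional Services Head Office and will be used for assessing rates of recidivism". The data-access section ({31c}), writing about future use, calls the corrections authority in each state the custodian of that dataset.

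Two further statements bear on release. The exclusion criteria remove "those prisoners due to leave prison within 16 weeks", and the Discussion says of less aggression: "This can contribute to reduced sentencing and time in custody".

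**The concern.** There are two separate issues.

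**Coverage.** The one database named for reoffending holds the court appearances of one of the two recruiting states. This is more than an omitted detail: the article says which source will be used, and that source cannot show a South Australian court appearance. Unless those men are taken out or another source is added, their reoffending is under-recorded. The reported recidivism rates would then be too low, and absolute differences between arms too small.

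**Analysis set.** Release comes after randomisation. If treatment changes who is released, or when, the released men in the two arms are no longer the groups that randomisation made comparable. A difference in recidivism among them could partly reflect who got out.

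At stake is a long-term outcome that the article lists among its secondary aims and hypotheses and refers to in its translation plans.

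**Working it through.** The article gives no sample size, target difference or power for recidivism, so there is no figure to reproduce. The check is a comparison of the text, then an illustration of size.

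**1. Is there a South Australian source elsewhere?** Table 1, the Data management section, the Confidentiality section and section {31c} say who handles the outcome and who holds the identities needed for linkage. None names a South Australian record of reoffending. Identities make linkage possible, but they are not an outcome record.

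**2. Size of the coverage gap.** Inputs:
- 2-year recidivism of 35% to 41% (Discussion).
- South Australian share of released men, s: not stated; assumed 1/6 to 1/2.
- Assumed for illustration: South Australian men have no ROD record, stay in the denominator and count as non-reoffenders; true rates are the same in both states; s is equal in both arms.

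Formulas:
- observed rate = true rate × (1 − s)
- observed difference = true difference × (1 − s)
- observed risk ratio = [p_T(1 − s)] / [p_C(1 − s)] = p_T / p_C

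| s | Observed for 35% | Observed for 41% | A true 10-point difference appears as | Loss |
|---|---|---|---|---|
| 1/6 | 29.2% | 34.2% | 8.3 | 17% |
| 1/3 | 23.3% | 27.3% | 6.7 | 33% |
| 1/2 | 17.5% | 20.5% | 5.0 | 50% |

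The risk ratio does not move. With an assumed 25% relative reduction from 35%, it is 26.25/35 = 0.75 at s = 0 and 17.5/23.3 = 0.75 at s = 1/3.

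**3. Miscounting compared with leaving these men out.** Take 180 per arm (the planned 360 completers halved, all released, which is optimistic), the same assumed 25% relative reduction from 35%, two-sided alpha of 0.05 and no allowance for clustering. Power = Φ[(d − 1.96·se0)/se1], with se0 the pooled and se1 the unpooled standard error.

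| s | Counted as non-reoffenders | Excluded |
|---|---|---|
| 0 | 43.7% | 43.7% |
| 1/6 | 35.4% | 37.5% |
| 1/3 | 27.8% | 31.1% |
| 1/2 | 20.9% | 24.5% |

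In this illustration, excluding men who cannot be followed costs less power than keeping them as non-reoffenders, and it does not dilute the rates. Power is low in every row, which suits an exploratory outcome.

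**4. Released-only denominator.** Men due out within 16 weeks are excluded, so planned release follows randomisation and treatment. The Discussion's remark on time in custody gives a route from treatment to release. The article gives no figure for that effect, so it cannot be sized.

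**The case against.** The best case against the point is that a journal article condenses a fuller plan, and that Head Office and the state corrections authorities leave a route open to South Australian data. That stands in part. It would be wrong to infer that those data will certainly be lost. What the text supports is that the source as written does not hold them.

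Other stronger readings are tempting, but the article does not support them:

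- **That South Australian men will be counted as non-reoffenders.** No coding rule is given. They could be treated as missing or out of scope, in which case sample size is lost and nothing is diluted.
- **That the gap favours one arm.** Randomisation is within centre, so under-recording should fall about equally on both arms. It shrinks absolute quantities and leaves the risk ratio roughly intact.
- **That recidivism drives the policy and cost case.** The Statistical methods section ties policy implementation to the IBOS and calls secondary outcomes hypothesis generating. The national saving quoted in the Discussion is costed per aggressive prisoner prevented, not from reoffending.
- **That men with unequal time at risk are mixed.** The article does not say so. Two years counted from each release would give similar follow-up; the starting point is simply not stated.

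It can also be said that reoffending in the community is visible only after release, and that an effect of a 16-week supplement on release is speculative. Both are fair. Some conditioning on release is inherent, so the released-only rate need not be abandoned, but it should not be read as a randomised comparison.

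**Conclusion.** The point holds in limited form. The named source covers NSW courts, the trial also randomises in South Australia, and nothing in the article supplies the missing state. If South Australian men are kept as non-reoffenders, absolute rates and differences shrink by their share: 17% to 50% for shares of 1/6 to 1/2. Both the coding and the share are assumptions. The risk ratio is roughly preserved, provided the share is similar among released men in both arms.

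The released-only denominator is a genuine post-randomisation subset with a route from treatment that the article itself suggests, of unknown size.

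Severity is low to moderate. Recidivism is tertiary in Table 1 (secondary in the aims and hypotheses) and is not powered. Neither the IBOS analysis nor the policy decision tied to it is touched.

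**What to change.** 1. Restrict the recidivism outcome to men randomised in NSW centres, or name an equivalent South Australian source before including men randomised there. Settle this before linkage.
2. State that the 2-year period starts at each man's release.
3. Report the number released and the time to release by arm.
4. Label the released-only comparison as descriptive. Add a supporting analysis of all eligible randomised men that accounts for time in custody.
5. If a fixed window from randomisation is used for that analysis, say what it measures. Men still in custody cannot reoffend in the community and earlier release adds exposure, so the window mixes any effect on release with any effect on reoffending.

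The cost is a few sentences of text and slightly more analysis. If South Australian men are excluded, the recidivism sample is smaller by their share.

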**Table 2 Tab2:**
[figure not shown]
Schedule of enrolment, intervention and assessments

^1^IBOS less than 1, blood clotting disorders, blood thinning medication, known medical condition, omega-3 index greater than 6% of total erythrocyte fatty acids

#### Health and quality of life (Table 1)

The validated SF-36 Quality of Life Questionnaire (adapted to suit prisoners) will be used to assess health-related quality of life. The adapted versions will include 3 questions on sleep. Muscle strength will be assessed by hand grip strength [59].

#### Assessment of blood samples (Table 1)

All blood samples will be transported from each site to the University of Wollongong (UOW). The erythrocytes will be stored in a minus 80 °C freezer at UOW prior to analysis. The erythrocyte fatty acids will be analysed in CIA BJM’s laboratory using standard techniques [7].

### Translation into policy and practice

Adapting ‘what works to promote evidence based practice’ [60], the overall objective is to create a scenario where, nationally, ex-prisoners continue adherence to omega-3 supplementation post-release, with the expectation that in doing so, maintenance of reduced recidivism rates will be achieved. For this to occur, there needs to be:

A framework for national incorporation of dietary supplementation within prison systemsAn educational programme for prisoners on the benefits of omega-3 supplementationAdherence to treatment practices and policies to overcome obstacles to continued effective ingestion of omega-3, including issues associated with cultural sensitivities.

#### A framework for national dietary supplementation

If a robust evidence base is established for the efficacy of omega-3 supplementation on behavioural improvement, attention enhancement and engagement in correctional rehabilitation, the first translational challenge is to disseminate the programme nationally. This will require, in the first instance, a framework for the dissemination of supplements across jurisdictions, accounting for health considerations (such as prisoner use of blood thinning agents as part of their medical treatment), leveraging the Corrective Services Advisory Committee and, in particular, the network of AI LG. To do this, dietary outcomes would need to first be linked to extant policies on prisoner nutrition (such as the Corrective Services Industries Food Services’ Nutrition Policy Statement, 2015), indicating the obligation for a minimum intake of omega-3-rich foodstuffs. Next, stakeholder dialogue of a National Round Table (NRT) of Corrective Services policy makers through the Corrective Services Administrators Council to agree on a Policy Statement on the minimum supplementation schedule to achieve clinical outcomes commensurate with the evidence base. A briefing document, containing all relevant information, would be provided to the stakeholders and real-time feedback sought to ensure a high response rate. Following the NRT, the research team could collaborate with key stakeholders to develop a tool-kit for rollout in each jurisdiction for ‘system readiness’ by involving and mobilising ground-level stakeholders, human resources and service infrastructure requirements, management systems and monitoring and evaluation systems.

#### Educational programme for prisoners

To effectively implement the programme, prisoners will need to be both consulted and educated about the range of health benefits associated with omega-3 supplementation. This will involve consultation with prisoner representative groups and cultural sensitivity advisors to establish a protocol for the dissemination of information. The delivery of the educational package will be modelled on the NSW Corrective Services ‘Healthy Survival Tips’ programme which involves a 4-h education programme on induction to prison with the SAPO (Services and Program Officer); a pre-release programme, integrated into programmes similar to the Corrective Services NSW ‘Nexus’; and the provision of written ‘brochure’ material on ‘Healthy Living Outside Gaol’ where omega-3 supplementation may be integrated into general health advice. Given the low level of formal education received (results from feasibility trial) and the associated lack of health literacy skills, in addition to the aforementioned educational packages, prisoners will also educate themselves and champion findings. For example, in the feasibility study, the prisoners did a rap video ‘Omega-3s are the key, they are good for you and good for me’.

#### Adherence to treatment practices and policies

Adherence to health interventions is a perennial problem across health contexts and is likely to be an issue with omega-3 supplementation. A broad range of adherence interventions exist. First and foremost, the fiscal cost of maintenance post-release will need to be addressed. To manage this, Commonwealth support similar to PBS schemes should be established. This would require liaison with the Federal Minister and/or his/her representatives informed by evidence of joint health and social system effect of omega-3 supplementation on violence and recidivism rates and related economic consideration of expected downstream health and social systems savings relative to investment [61–64] in omega-3 supplements in prison populations. Advocacy for a ‘Health Care Card’ system where purchase of prescribed omega-3 supplements by former prisoners is subsidised could be sought. Additionally, with positive findings post-release, supervision policies could be negotiated at the federal and state level (incorporated in discussions under ‘National Framework’ above) whereby adherence issues are resolved at a prisoner by prisoner level. A brief training video would also be disseminated to Probation and Parole offices via YouTube to enhance adherence management skills relevant to omega-3 intake.

#### Authorship

It is anticipated that all authors on the protocol paper will also be authors on the primary outcome paper.

### Participant timeline {13}

Participant timeline is shown in Table 2.

### Sample size {14}

Our study is a randomised controlled trial powered to show a difference between treatment and placebo control of 25% in the proportion of participants experiencing a reduction in aggressive behaviour as measured by a change in the IBOS. Given the nature of the prison populations, it is likely that there will be an effect of prison in the analysis, and therefore, a design effect accounting for the intra-cluster correlation is incorporated in the sample size estimation with a conservatively estimated ICC of 0.03. Based on our pilot data, we anticipate that attrition will likely be high (~ 40%) with the sample size for recruitment appropriately inflated to account for this. Overall, a total sample size of 600 with 360 completing the study enables a difference of 25% to be detected with 80% power and an alpha level of 0.05.

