## Assignment of interventions: allocation

### Sequence generation {16a}

Participants will be block randomised (according to their IBOS, age and baseline omega-3 index) within each treatment centre to one of the 2 study arms. The randomisation will be performed by Chief Investigator MB (biostatistician) using the RALLOC command in STATA V12 or higher (College Station, TX).

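### The sample size includes a cluster design effect for prison that individual randomisation within prisons does not call for, so the stated 80% power for 25% is conservative: read as percentage points, 360 completers give over 99%

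*Protocol article*

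**What the plan says.** All references are to the protocol article.

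- Sample size {14} describes a trial "powered to show a difference between treatment and placebo control of 25% in the proportion of participants experiencing a reduction in aggressive behaviour". It expects an effect of prison and for that reason says that "a design effect accounting for the intra-cluster correlation is incorporated in the sample size estimation with a conservatively estimated ICC of 0.03". After allowing for about 40% attrition, it concludes that "a total sample size of 600 with 360 completing the study enables a difference of 25% to be detected with 80% power" at an alpha of 0.05.
- Trial design {8} sets 1:1 allocation.
- Sequence generation {16a} says: "Participants will be block randomised (according to their IBOS, age and baseline omega-3 index) within each treatment centre". The unit of randomisation is therefore the prisoner, and both arms are present in every prison.
- Statistical methods {20a} plans a generalised linear mixed model for the responder proportion, adjusted for clustering by prison.
- Study setting places the trial "in at least 6 Correctional Centres".

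**The concern.** The usual inflation, 1 + (m − 1) × ICC, is for trials that allocate whole clusters. There, differences between prisons are mixed up with the difference between arms. Here each prison holds both arms, so whatever raises or lowers response in a prison does so for both. The reason given for the inflation, an effect of prison, does not apply to the treatment contrast in this design.

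What is at stake is the accuracy of the main power statement. It tells a reader that 360 completers are needed to detect 25% with 80% power. If the inflation is not needed, the trial is far more sensitive than that, and the detectable difference is overstated by about 10 points.

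**Working it through.** **Inputs.** From Sample size {14}: difference 25%, power 80%, alpha 0.05, ICC 0.03, attrition about 40%, 360 completers of 600. From Trial design {8}: 1:1, so 180 completers per arm. Assumed because the article does not state them: a two-sided test, 25% as percentage points, placebo rates from 5% to 70%, and six equal prisons of 360/6 = 60 completers.

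**1. Reproducing the plan's figure.** Completers per arm for two proportions:

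n = [1.96 √(2 p̄(1 − p̄)) + 0.8416 √(p₁(1 − p₁) + p₂(1 − p₂))]² / (p₂ − p₁)²

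For 37.5% v 62.5%: [1.96 × 0.7071 + 0.8416 × 0.6847]² / 0.0625 = 61.6, so 62 per arm or 124 in total.

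Design effect with m = 60: 1 + 59 × 0.03 = 2.77.

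- 124 × 2.77 = 343 completers. At 360 completers the effective number is 360/2.77 = 130, and power is 82%.
- With continuity correction, 25% v 50% or 50% v 75% needs 66 per arm: 132 × 2.77 = 366.
- 360/(1 − 0.4) = 600 exactly.

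The stated 360 is thus approximately recovered with the cluster inflation. Without any design effect, the largest total for a 25-point difference is 124 (140 with continuity correction).

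**2. Variance under the design described.** Take an outcome made up of a prison effect with share ICC of the variance, a treatment effect, and individual variation.

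- Whole prisons randomised: variance of the contrast is multiplied by 1 + (m − 1) × ICC = 2.77.
- Prisoners randomised within prisons, with prison in the model: the prison term drops out of each within-prison difference, leaving a factor of about 1 − ICC = 0.97.

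**3. Power without the inflation, 180 per arm.** For 37.5% v 62.5%:

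z = (0.25 × √180 − 1.96 × 0.7071) / 0.6847 = (3.354 − 1.386) / 0.6847 = 2.87, so power is 99.8%.

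This is the lowest value over the placebo rates tried. The difference detectable with 80% power is:

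| Placebo rate | No design effect | With 2.77 |
|---|---|---|
| 20% | 13.0 points | 22.6 points |
| 30% | 14.2 | 24.0 |
| 40% | 14.7 | 24.3 |
| 50% | 14.6 | 23.7 |
| 70% | 12.5 | 19.6 |

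For 25 points at 80% power, about 124 completers suffice, or 124/0.6 = 207 recruited. 360/124 = 2.9.

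**4. Simulation.** Six prisons, 30 per arm in each, ICC 0.03, Cochran-Mantel-Haenszel test, 20,000 runs. Power is 99.8% for 37.5% v 62.5% and 82.5% for 42.5% v 57.5%. Type I error is 5.0%.

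If the treatment effect itself varies between prisons with an SD of 5, 10 or 15 points, power for 25 points is 99.6%, 98.9% and 97.1%. For 15 points it is 80.6%, 76.5% and 73.6%.

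**5. If 25% were relative.** 50% v 62.5% has 67% power with 180 per arm and no design effect, and 30% with the factor of 2.77. Over base rates of 20% to 80%, relative differences with that factor need from 454 to 6,061 completers, so this reading does not give 360 together with the stated ICC.

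**The case against.** The strongest reply is that the error is on the safe side. On the percentage-point reading, the claim that 360 completers can detect 25% with 80% power is true as a floor. No test, estimate or recruitment target is wrong because of it. This stands, and it limits the importance of the point.

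The factor of 2.77 is also an inference. The article gives no cluster size and speaks of a minimum of six centres. With eight equal prisons, m = 45 gives 2.32 and 124 × 2.32 = 288. With 600/6 = 100 per prison, the factor is 3.97 and the total 492. This stands too, but the results without a design effect do not depend on it.

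A design effect could be defended as cover for treatment effects that differ between prisons. The section gives only an effect of prison as its reason, and variation of the size simulated leaves power for 25 points at 97% or more. It does lower power for 15 points.

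A reader might infer more than the article supports:

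- *That the trial is underpowered or should change size.* This would follow only if 25% were relative. The wording of Sample size {14}, a difference in a proportion, favours percentage points. The Discussion does use 25% relatively (25% of 34% = 8.5%), so the scale needs confirming, but that does not show a shortfall.
- *That the unstated placebo responder rate is itself a fault.* An article may leave it to the full protocol, and the conclusion holds over the range tried.
- *That a null result would be misread, or that recruitment decisions would go wrong.* The article contains no such reading or decision rule. What a result excludes depends on its confidence interval.

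**Conclusion.** The concern holds as an overstated sample size requirement. A cluster design effect justified by a prison effect does not belong to a trial that randomises individuals within prisons and adjusts for prison. With 25% as percentage points, a two-sided 5% test and an effect that is the same in every prison, 360 completers give over 99% power for 25 points and 80% power for at most about 15 points. About 124 completers would give the stated 80% for 25 points.

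These figures hold for every placebo rate tried. That the plan used a factor near 2.77 is plausible but not shown. Because the error is conservative, this is a correction to the power statement and no threat to the trial's validity.

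**What to change.** Revise the paragraph in Sample size {14}:

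1. Remove the cluster design effect, or keep it and label it a conservative allowance that randomisation within prisons does not require.
2. Confirm that 25% is an absolute difference in responder proportion. If a relative difference was meant, the power has to be recalculated from the assumed placebo rate.
3. If it is absolute, restate the power, for example:

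> Prisoners are individually randomised within prison and the model adjusts for prison. With 360 completers and a two-sided 5% test, power exceeds 99% for the target difference of 25 percentage points and is 80% for a difference of about 15 points, assuming a similar effect in all prisons.

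The 25-point target difference stays as the planned effect, and the targets of 600 recruited and 360 completing are unchanged. The cost is the wording of one paragraph, with no extra participants and no change to the analysis.
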